### **Statement of Compliance**

This study will be conducted in compliance with all stipulation of this protocol, the conditions of the ethics committee approval, the NHMRC National Statement on ethical Conduct in Human Research (2007) and the Note for Guidance on Good Clinical Practice (CPMP/ICH-135/95).

## STUDY SYNOPSIS

(please provide brief information)

|                      |                                                                                                                                                                                                                                                                                                                                                                                                                  |
|----------------------|------------------------------------------------------------------------------------------------------------------------------------------------------------------------------------------------------------------------------------------------------------------------------------------------------------------------------------------------------------------------------------------------------------------|
| Title:               | A randomised trial of focused cardiac, lung, and femoral and popliteal vein ultrasound on the length of stay in internal medicine admissions with a cardiopulmonary diagnosis – the IMFCU 1 study                                                                                                                                                                                                                |
| Short Title:         | IMFCU 1 study                                                                                                                                                                                                                                                                                                                                                                                                    |
| Design:              | RCT                                                                                                                                                                                                                                                                                                                                                                                                              |
| Study Centres:       | Melbourne Health - RMH campus                                                                                                                                                                                                                                                                                                                                                                                    |
| Hospital:            | RMH                                                                                                                                                                                                                                                                                                                                                                                                              |
| Study Question:      | Does physician performed focused cardiac, lung, and femoral and popliteal vein ultrasound reduce length of stay by at least 24 hours, for internal medicine admissions with a cardiopulmonary diagnosis?                                                                                                                                                                                                         |
| Study Objectives:    | To identify whether focused cardiac, lung, and femoral and popliteal vein ultrasound performed within 24 hours of hospital admission reduced length of stay in a cohort of patients with a cardiopulmonary admission diagnosis.                                                                                                                                                                                  |
| Primary Objectives:  | Length of stay $\geq$ 24 hours defined clinical significance                                                                                                                                                                                                                                                                                                                                                     |
| Secondary Objectives | Time and cost analysis on major investigations and diagnoses prior to establishment of the definitive diagnosis

Health economic analysis                                                                                                                                                                                                                                                                  |
| Inclusion Criteria:  | Participants will be considered for inclusion if they meet all of the following criteria: 
 
• Adult participants (<math>\geq</math>18 years) with a cardiopulmonary diagnosis.
 
• Admitted to a general medical unit at the Royal Melbourne Hospital
 
• Able to provide informed consent
 
• Expected to remain in hospital >24 hours.
 
 |
| Exclusion Criteria:  | Participants will be excluded if they meet any of the following criteria: 
 
• admitted >24 hours
 
• admitted for social rather than medical reasons
 
                                                                                                                                                                                                   |

**Study Name:** A randomized trial of focused cardiac, lung, and femoral and popliteal vein ultrasound on the length of stay in internal medicine admissions with a cardiopulmonary diagnosis – the IMFCU 1 study

**Protocol Number:** 2018.200

**Version & date:** version 1 dated 20 May 2018

Page 5 of 18

|                             |                                                                                                                                                                                                                                                                                                                                                                                                                                                                                                                                                                                                                                                                                                                                                                                                                                      |
|-----------------------------|--------------------------------------------------------------------------------------------------------------------------------------------------------------------------------------------------------------------------------------------------------------------------------------------------------------------------------------------------------------------------------------------------------------------------------------------------------------------------------------------------------------------------------------------------------------------------------------------------------------------------------------------------------------------------------------------------------------------------------------------------------------------------------------------------------------------------------------|
|                             | 
 
• unable to provide consent
 
• contact or respiratory isolation
 
• transthoracic echocardiogram within 4 weeks prior to admission
 
• CT chest scan during the admission process prior to enrolment
 
                                                                                                                                                                                                                                                                                                                                                                                                                                                                                                                                                         |
| Number of Planned Subjects: | 250                                                                                                                                                                                                                                                                                                                                                                                                                                                                                                                                                                                                                                                                                                                                                                                                                                  |
| Investigational product:    | N/A                                                                                                                                                                                                                                                                                                                                                                                                                                                                                                                                                                                                                                                                                                                                                                                                                                  |
| Safety considerations:      | The focused cardiac, lung and vein ultrasound is non-invasive and does not present risk to the patient                                                                                                                                                                                                                                                                                                                                                                                                                                                                                                                                                                                                                                                                                                                               |
| Statistical Methods:        | 
The outcome of interest, hospital length of stay (LOS), is expected to be skewed and hence will be log transformed for the purposes of analysis. Control data were available for Q4 2017, with a mean log based 10 LOS of 2.01 (equivalent to 103 hours on the original scale) and a standard deviation of 0.36. In this study censoring will not be applied to the LOS. The primary outcome will be tested using Student t-test on the log-transformed LOS data.
 
In order to detect a clinically important reduction in LOS of 24 hours for the ultrasound group, based on the expected control value above and a common standard deviation on the log scale, power of 0.8 and size 0.05, 122 participants are required in each of the two treatment groups, which will be rounded up to a total of 250 participants.
 |
| Subgroups:                  | 
Standard care: no focused ultrasound is performed. Diagnosis and management decisions will be recorded prospectively.
 
Intervention group: Within 24 hours of admission to hospital, the researcher will perform a focused cardiac, lung, and femoral and popliteal vein ultrasound. The findings will be revealed to the medical team after they have completed a diagnosis and management form. Thereafter, all management is directed by the treating medical team and specifically, the intervention will not provide any management guidelines.
                                                                                                                                                                                                                                                                    |

## 1. GLOSSARY OF ABBREVIATIONS & TERMS

| Abbreviation       | Description (using lay language)                                                                                                     |
|--------------------|--------------------------------------------------------------------------------------------------------------------------------------|
| FCU                | Focused cardiac ultrasound – a goal focused heart ultrasound (echocardiography) performed at the patient bedside                     |
| Hospital Admission | Time from acceptance of admission to hospital (if admitted via ED), or arrival in the ward (if directly admitted from the community) |
| LOS                | Length of stay- the number of hours a patient remains in hospital                                                                    |

## 3. INTRODUCTION/BACKGROUND INFORMATION

### 3.1 LAY SUMMARY

When patients are admitted to hospital, they undergo clinical evaluation by the doctor, and then may undergo tests. Clinical evaluation alone is known to be inaccurate in up to 50% of patients with suspected heart or lung disease. Ultrasound is a non-invasive test that can improve the accuracy of clinical evaluation. We will study whether use of heart, lung, and femoral and popliteal vein ultrasound performed at the patient bedside in addition to clinical evaluation can lead to a reduced length of stay in hospital, as well as shorten the time and number of tests performed, prior to the definitive diagnosis being made. The study will be

---

**Study Name:** A randomized trial of focused cardiac, lung, and femoral and popliteal vein ultrasound on the length of stay in internal medicine admissions with a cardiopulmonary diagnosis – the IMFCU 1 study

**Protocol Number:** 2018.200

**Version & date:** version 1 dated 20 May 2018

Page 7 of 18

randomised (like flipping a coin) to compare “standard care” which does not routinely include ultrasound examination with the use of heart, lung and lower extremities veins ultrasound performed within 24 hours of admission to hospital.

### 3.2 INTRODUCTION

Internal medicine is well-known for its complexity. Most of the patients are elderly, with many comorbidities and requiring multiple medications. Typically, internal medicine physicians rely on the medical history and physical examination, collectively known as “clinical evaluation”, to derive a differential diagnosis and initial management plan.

However, it is known that clinical evaluation alone is frequently inaccurate in determining the correct diagnosis. Incorporating a basic ultrasound examination performed at the patient’s bedside, in addition to clinical evaluation increases diagnostic accuracy.(1, 2, 3, 4) This technique is termed “focused ultrasound” or “point-of-care ultrasound” and has become increasingly popular among other specialties such as anaesthesia and critical care. The admission diagnosis where addition of focused ultrasound examination may be most beneficial, is the “cardiopulmonary diagnosis” as it is frequently difficult to separate the cause of symptoms such as shortness of breath or collapse to either a cardiac or respiratory problem. Further, deep vein thrombosis may cause pulmonary embolus, but clinical evaluation for deep vein thrombosis is inaccurate. Although it is likely that focused ultrasound examination will improve diagnostic accuracy, which in turn will alter management decisions, there are no data identifying whether that will result in improved clinical outcomes such as length of stay.

### 3.3 BACKGROUND INFORMATION

Most of the literature has been performed in the settings of anaesthesia, critical care and emergency medicine. The outcomes are predominantly related to diagnostic and management changes. Heiberg et al.(5) have published a systematic review of use of focused cardiac ultrasound (FCU) in non-cardiac surgery anaesthesia and intensive care and reported a 41 - 51% change in diagnosis or management after FCU was performed. In anaesthesia, when it was performed as part of the pre-operative evaluation for a non-cardiac surgery, change in management was seen in 12% of asymptomatic patients if it was used as a screening tool, and between 54% and 82% when it was performed in participants suspected of having heart disease. In the emergency department, the use of focused ultrasound assessing heart, lungs, abdomen and/or lower limb veins led to a change in the primary diagnosis in 32.2% of patients and management plan in 50%.(6) In some life threatening scenarios the impact is even higher. A change in therapy has been described in 89% of patients during a cardiopulmonary resuscitation(7), and an increase in accuracy for the correct diagnosis from 50% to 80% in patients with non-traumatic undifferentiated hypotension.(8)

Most of the literature investigates the use of focused cardiac ultrasound. However, the use of lung ultrasound has gained popularity, and is increasingly recognised as an useful diagnostic tool for the diagnosis of pneumonia, pneumothorax, pleural effusion and cardiogenic pulmonary oedema.(9-11) It is a helpful tool for rapidly identifying the aetiology of acute respiratory failure, and has a role in prognostic assessment in the intensive care setting, as underlying lung pathology is associated with ventilation time and mortality.(12) A 2-point compression ultrasound of the lower extremity vein has an excellent accuracy in the

detection of proximal deep venous thrombosis(13) and is becoming increasingly utilised as a bedside test in emergency medicine. This method involves merely femoral and popliteal vein examination, as the presence of isolated thrombi in proximal veins other than these two is very unlikely.(14)

Surprisingly, there are few data available in the internal medicine (general medicine) setting. Croft et al.(15) published a pilot study in internal medicine outpatients, in which adding a focused cardiac ultrasound to the standard evaluation altered diagnostic testing or medical therapy in 40% of the cases. Although there is good evidence for improved diagnostic accuracy of focused ultrasound in addition to clinical evaluation, and that leads to management changes, there are very few studies examining whether clinical outcomes such as mortality, morbidity or length of stay are improved by the use of focused ultrasound examination. From our research group, Canty DJ. et al. (16) published a pilot randomised trial in patients with hip fracture, in which focused cardiac ultrasound performed as part of the preoperative evaluation appeared to reduce the incidence of composite outcome of death, cardiac and renal complications by 39%. However, the study was a pilot study used to inform effect size and feasibility for a definitive pragmatic RCT, rather than provide a definitive answer.

It is plausible that improving diagnosis and altering management plans, may lead to improvement in the work flow and reduce of the length of hospital stay. There is limited data available to answer this question, but in emergency medicine a significant reduction in the emergency department length of stay was reported in two studies after the implementation of training programmes in point-of-care ultrasound.(17, 18) A further example is in patients with clinically important pericardial effusion, where a focused cardiac ultrasound in the emergency department reduced the time from presentation to pericardiocentesis from 70.2 to 11.3 hours. (19)

The patients who are admitted to general medical wards are often elderly with multiple comorbidities. There are very few data investigating the use of focused ultrasound in this population. However, it is plausible that that these patients will not be that different from the emergency department, anaesthesia or intensive care populations, such that adding focused ultrasound to clinical evaluation is likely to alter diagnosis and management. Furthermore, it is plausible that if the correct diagnosis is made earlier in the admission time course, then length of stay could also be reduced. Improvements in workflow could also lead to reduced cost. In a general medical population with a “cardiopulmonary” admission diagnosis, the focused ultrasound may help to define whether the presenting problem is cardiac or respiratory in origin. By adding femoral and popliteal vein ultrasound, we can identify presence of proximal deep venous thrombosis, which could cause pulmonary embolus and explain patient symptoms, but also the finding of a vein thrombus by itself is clinically relevant as denotes change in the patient therapy and in some cases further studies to determine the aetiology. When routine ultrasound screening has been performed, 4.5 % of patients have an asymptomatic proximal deep venous thrombosis at the time of admission to the internal medicine ward.(20)

We aim to investigate whether use of focused cardiac, lung, and femoral and popliteal vein ultrasound in addition to clinical evaluation can reduce hospital length of stay. We will further aim to identify mechanisms such as time to definitive diagnosis, work flow and health care costs arising from investigations and bed stay.

## 4. STUDY OBJECTIVES

### 4.1 HYPOTHESIS

The addition of focused cardiac, lung, and femoral and popliteal vein ultrasound to clinical evaluation will reduce the length of stay by at least 24 hours in a cohort of internal medicine patients with an admission diagnosis of a cardiopulmonary disease and expected to stay in hospital > 24 hours.

### 4.2 STUDY AIMS

To identify whether focused cardiac, lung and femoral & popliteal ultrasound to clinical evaluation:

- a. Reduced length of stay
- b. Shortens the time to definitive diagnosis
- c. Reduced the number of imaging or pathology tests performed prior to the definitive diagnosis is made
- d. Identifies >10% of new significant heart or lung pathology
- e. Is cost effective

### 4.3 OUTCOME MEASURES

- A. Primary outcome: length of stay measured in hours from the time of admission to the medical unit until discharge from the hospital
- B. Secondary outcomes
  - a. Time from admission to establishment of the definitive diagnosis (hours)
  - b. The frequency and type of new cardiopulmonary diagnoses that were not diagnosed prior to performance of the FCU and Lung ultrasound
  - c. The number and type of imaging and pathology investigations performed prior to establishment of the definitive diagnosis.
  - d. Cost will be based on bed stay and investigation costs for the Royal Melbourne Hospital
  - e. The proportion of participants where imaging cannot be obtained.

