  - b. The treating medical staff (at least registrar level) will complete a custom diagnostic and management form on a daily basis (see CRF). Change in the custom form fields will be used to identify change.
  - c. The number and type of tests will be identified from hospital records including online pathology and radiology services.

- d. The definitive diagnosis will be reported by the treated medical team. The diagnosis will be verified against the discharge diagnosis.
  - e. All FCU lung, and femoral vein ultrasound images will be recorded in DICOM format. The images and report forms will be checked by an independent expert, as a quality assurance of the accuracy of the bedside ultrasound. Furthermore, if the participant undergoes comprehensive echocardiography or lung ultrasound or CT scan, the finding of the bedside examination will be cross checked against the formal investigations.
7. Time frames: participants will be enrolled within 24 hours of hospital admission and follow up concludes at hospital discharge.
  8. No home visits

This protocol will be used as part of a Master of Medicine degree for [name] [name] at the University of Melbourne.

9. Provide a flowchart or table specifying visits, interventions and other relevant details

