### 8.2 POWER CALCULATIONS

The outcome of interest, hospital length of stay (LOS), is expected to be skewed and hence will be log transformed for the purposes of analysis. Control data was available from 2017, with a mean log based 10 LOS of 2.01 (equivalent to 103 hours on the original scale) and a standard deviation of 0.36.

In order to detect a clinically important reduction in LOS of  $\geq 24$  hours for the ultrasound group, based on the expected control value above and a common standard deviation on the log scale, power of 0.8 and size 0.05, 122 patients are required in each of the two treatment groups, which will be rounded up to a total sample size of 250 participants.

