### **1) Health costs:**

If the health costs data is skewed, it will be log-transformed to normalise its distribution and analysed using Student's t-test.

- 2) 30-day readmission data will be presented as dichotomic data and analysed using Fisher exact test.
- 3) The impact of FCU on the diagnosis and management will be reported in the intervention group only describing the number and proportion of participants.

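### As written, the cost outcome covers only the index admission, so the cost comparison for aim e cannot register bed hours spent or saved through readmission in the 30 days the analysis plan already examines

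*Protocol*

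**What the plan says.** Aim e in section 4.2 asks whether adding ultrasound "Is cost effective". The outcome that serves it, section 4.3 B.d, reads "Cost will be based on bed stay and investigation costs for the Royal Melbourne Hospital". Section 3.3 names the same two components: "work flow and health care costs arising from investigations and bed stay". None of these states how long costs are counted.

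The protocol's end of follow-up is in section 5.1 item 7: "participants will be enrolled within 24 hours of hospital admission and follow up concludes at hospital discharge". The study table also stops at the discharge day. The only stay defined as an outcome is the primary one in section 4.3 A: "length of stay measured in hours from the time of admission to the medical unit until discharge from the hospital".

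The statistical analysis plan at the end of the document deals with cost and readmission as separate items. On cost: "If the health costs data is skewed, it will be log-transformed to normalise its distribution and analysed using Student's t-test". On readmission: "30-day readmission data will be presented as dichotomic data and analysed using Fisher exact test". Readmission is not among the outcomes in section 4.3.

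**The concern.** Two end points of follow-up are in force: index discharge in section 5.1, and 30 days in the analysis plan. A 30-day readmission cannot be observed if follow-up has ended at discharge, so these statements need reconciling in any case. The cost outcome appears to follow the shorter one.

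That matters because the hypothesised effect is earlier discharge. A cost that stops at discharge credits each hour of earlier discharge as a saving. It cannot show whether some of those hours are spent again on patients who return. Nor can it show further hours saved if earlier correct diagnosis, the mechanism put forward in section 3.3, keeps patients from returning. What is at stake is the cost-effectiveness conclusion, in either direction.

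**Working it through.** **What the sections imply together**

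- Components of cost: bed stay and investigations at one hospital (4.3 B.d).
- Bed stay as measured: ends at discharge (4.3 A; 5.1 item 5 lists hospital length of stay and tests, with no stay after discharge).
- Follow-up: ends at discharge (5.1 item 7).
- Health costs item of the analysis plan: a transformation and a test, with no horizon and no mention of readmission.
- Readmission item: yes/no only, so it yields neither bed hours nor tests that could be priced.

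Followed as written, cost is priced on the index admission. This is an inference from the five items together; no single sentence says it.

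**The plan's own figure**

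Section 8.2 describes control stays "with a mean log based 10 LOS of 2.01 (equivalent to 103 hours on the original scale) and a standard deviation of 0.36". Check: 10^2.01 = 102.3 h, and log10(103) = 2.013, so 103 h agrees within rounding. The documents give no figure for cost, readmission rate or readmission stay.

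**Planned saving in mean bed time**

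Total bed cost depends on the arithmetic mean. I assume a lognormal stay and apply no truncation.

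- Control mean = 10^2.01 × exp((0.36 × ln 10)² / 2) = 102.3 × 1.41 = 144.3 h.
- The planned 24 h reduction takes 103 h to 79 h, with a common SD on the log scale. Mean saving = 144.3 × (1 − 79/103) = 33.6 h per patient.

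**Offset if readmission differs**

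Offset per randomised patient = difference in readmission risk × mean readmission stay. Break-even = 33.6 h / mean readmission stay. Both the risk difference and the readmission stay are assumed.

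| Assumed readmission stay | 5-point excess | 10-point excess | Break-even excess |
|---|---|---|---|
| 72 h | 3.6 h (11%) | 7.2 h (21%) | 33.6/72 = 47 points |
| 144.3 h (as the control index mean) | 7.2 h (21%) | 14.4 h (43%) | 33.6/144.3 = 23 points |
| 168 h | 8.4 h (25%) | 16.8 h (50%) | 33.6/168 = 20 points |

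Percentages are of 33.6 h. With no difference in readmission the offset is zero. With fewer readmissions under ultrasound the sign reverses, and the index-admission cost understates the saving.

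**Would the yes/no comparison reveal it?**

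With 125 per arm and an assumed control readmission rate of 10% to 20%, the power of a two-sided 5% comparison (normal approximation) is about 22% to 16% for a 5-point excess and about 60% to 45% for a 10-point excess. A non-significant result would therefore be weak reassurance about cost.

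**The case against.** The strongest case against runs as follows. Section 4.3 B.d gives components and a hospital, not a horizon, and a second stay at the same hospital is still a bed stay there. Index-admission cost with readmission reported beside it is a recognisable hospital-perspective choice. The analysis plan promises 95% confidence intervals for all estimates, so a rise in readmissions would be visible next to the cost result. Nothing in the documents suggests that readmissions will rise: discharge is decided by the treating team, and the stated mechanism is earlier correct diagnosis. Most of the planned saving would survive a modest excess.

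Much of this stands. The exclusion is inferred, and the sign of any bias is unknown. A reader might infer that the plan overstates the saving from ultrasound. The documents do not support that, because it would be true only if readmissions rose in that arm. A reader might also take all unpriced readmission hours as the error. At an assumed 10% to 20% readmission rate and a 144.3 h stay, these are 0.10 × 144.3 = 14 h to 0.20 × 144.3 = 29 h per patient in each arm. If rate and stay are the same in both arms, those hours cancel in the cost difference and are not bias.

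What does not stand is that reporting readmission separately settles the matter. A yes/no count carries no bed hours, it is imprecise at this sample size, and aim e calls for a statement about cost effectiveness, not only about the cost of the first stay.

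**Conclusion.** The point holds in a conditional form. Read together, the outcome definition, the follow-up rule and the analysis plan confine cost to the index admission. The cost difference for aim e is then biased if readmission differs between arms: in favour of ultrasound if readmissions rise, against it if they fall, and unbiased in this respect if they do not differ.

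The size cannot be derived from the documents. The illustrative range is an offset of about 11% to 25% of the planned 33.6 h mean saving at a 5-point excess and about 21% to 50% at 10 points. It rests on assumed readmission stays of 72 to 168 h, assumed excess rates, and a lognormal stay with the plan's mean and SD. This concerns a secondary outcome; the primary length-of-stay test is unaffected.

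**What to change.** 1. Reconcile section 5.1 item 7 with the readmission item of the analysis plan, so that follow-up for readmission and cost ends 30 days after discharge.
2. In section 4.3 B.d and the Health costs item, define cost for aim e, per randomised patient, as index bed-stay and investigation costs plus those of any Royal Melbourne Hospital readmission within 30 days of discharge.
3. Show the index-admission cost alongside, labelled as such.
4. State that readmissions to other hospitals are not captured. The extended cost therefore reduces the problem without removing it entirely.

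The cost is small. Readmitted patients must already be identified for the planned readmission comparison. The added work is extracting their stays and tests; the analysis plan does not name its source for readmission, but the hospital records and the online pathology and radiology services of section 5.1 item 6 should serve for returns to the same hospital. The other downsides are a somewhat more variable cost figure and an amendment to the wording on follow-up.
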